## 1.7 Diagram of study procedures

### Intervention

### Assessment

#### Randomization

Dose 1 i.v.

[figure not shown]

\*

3 h

Dose 2 i.v.

[figure not shown]

12-18 h

Dose 3 i.v.

[figure not shown]

36-42 h

8-10 d

36/7 gest.  
weeks

Discharge  
home

40 weeks

24 months  
corrected

**A1:** Entry criteria, Apgar, CRIB,  
Placenta histology, blood count,  
cereb. Ultrasound

**A2:** Complications, cereb.  
ultrasound, blood  
count (

**A3:** Complications, eye  
exam, cereb. ultrasound,  
growth, blood pressure,  
oxygen need

**A4:** length of stay, CPAP days,  
days on respirator days,  
days on oxygen

**MRI (optional)**

**A5:** BSC II: MDI, PDI,  
neurol. exam, growth

[figure not shown]

## 2. Introduction

### Summary

#### Hypothesis

Early administration of human erythropoietin (EPO) in very preterm infants reduces perinatal injury to the brain (retina), lung and gut and improves neurodevelopmental outcome at 24 months corrected age.

#### Primary objective

To determine whether cerebral outcome is improved if infants born between 26 /7 and 31 /7 gestational weeks at birth receive erythropoietin in high dose in the first three days after birth.

#### Secondary objectives

To determine whether early administration of EPO alters the incidence of complications typically associated with preterm birth, i.e. mortality, septicaemia, necrotising enterocolitis, bronchopulmonary dysplasia (oxygen dependency at 36 weeks postmenstrual age), retinopathy, intracranial haemorrhage, white matter disease (periventricular leucomalacia), growth failure, cerebral palsy and handicap at 5 years.

#### Rationale

EPO has been shown to be protective against hypoxic-ischaemic and inflammatory injuries in a broad range of tissues and organs besides promoting red cell formation. It has been shown to have neuroprotective and neurotrophic activity in animals after acute brain damage as well as in adult stroke patients. Several mechanisms explaining this activity have been recognized: EPO inhibits glutamate release in the brain, modulates intracellular calcium metabolism, induces the generation of anti-apoptotic factors, reduces inflammation, decreases nitric oxide-mediated injury, and has direct antioxidant effects.

Very preterm infants have significant delay in mental and physical development assessed at 24 months corrected age. The most critical period are the first days after preterm birth where the oxygenation of the brain may be impaired by respiratory, circulatory and nutritional insufficiency. Although there are probably several mechanisms involved in permanent brain damage, it is most likely that EPO with its multiple action may reduce this damage.

EPO has been studied in several trials in preterm infants to prevent anaemia and is now widely used for this indication.

#### Study design

Randomized, double-masked, placebo-controlled multi-center clinical trial.

#### Research plan

420 infants will be randomized during the first three hours of life to receive EPO (3000 U/kg body weight) or placebo intravenously at 3, 12-18 and 36-42 hours after birth. Standardized evaluation including cerebral sonography at day 1 and 7-10 and at 36 /7 gestational weeks (or at discharge home if discharged before) will determine the presence or absence of complications. Cerebral volume and white matter volume will be assessed at 40 postmenstrual weeks with MRI (only if available).

Experienced examiners will assess developmental function at 24 months corrected age using the reliable and validly revised Bayley Scales II of Infant Development and determine the presence or absence of impairment of motor function (cerebral palsy) and neurosensory function (blindness or deafness).

At 5 years corrected age KaufmannABC II (a standardized neuropsychological test), neurological examination (cerebral palsy), visual and hearing examination, growth assessment and a questionnaire on child behavior will be used.

### **Clinical significance**

At least 1 of every 100 liveborn infants is born very preterm. 90% of these infants survive but >50% have a delay in mental and physical development assessed at 24 months corrected age. More subtle problems affecting cognition, vision and hearing are common at the age of five years and have an impact on school performance and quality of life of the infants and their families. The aim of this trial is to examine whether a short, easily applicable and well tolerated pharmacological intervention can improve neurodevelopmental outcome.

## **2.2 Background**

At least 1 of every 100 live born infants are very preterm. 90% of these infants survive, but the incidence of complications such as intracranial haemorrhage, periventricular leukomalacia, necrotizing enterocolitis, bronchopulmonary dysplasia, persistent ductus arteriosus and septicaemia is high. A considerable proportion of the afflicted infants develop cerebral palsy, delayed mental development and visual impairment when assessed at 24 months corrected age. More subtle problems affecting cognition, vision and hearing are common at the age of five years and have an impact on school performance and quality of life. The aim of this study is to examine, whether a short, easily applicable and well tolerated pharmacological intervention can improve outcome of important complications of prematurity.

### **2.2.1 Cell Culture and Animal Experiments**

EPO is a haematopoietic growth factor and cytokine which stimulates not only erythropoiesis but also has a critical role in the development, maintenance, protection and repair of the nervous system as well of other organs. A wide variety of experimental studies have shown that EPO and its receptor are expressed in the central nervous system and EPO exerts remarkable neuroprotection in cell cultures and animal models of nervous system disorders. The same is true for protective effects in other organs. The current knowledge on the mechanisms by which EPO produces neuroprotection and the signal transduction system regulated by EPO in the nervous system are summarized in two recent reviews.

The most relevant facts for the proposed study are briefly summarized: Studies in rats and primates showed that EPO in high dose crosses the blood brain barrier and has neuroprotective and neurotropic activity. Several mechanisms explaining this activity have been recognized: EPO inhibits glutamate release, modulates intracellular calcium metabolism, induces the generation of neuronal anti-apoptotic factors, reduces inflammation, decreases nitric oxide-mediated injury, and has direct antioxidant effects. The most often used animal model are rats in whom several research groups could demonstrate a significant decrease in infarct volume after a hypoxic-ischaemic insult and an improvement in task resolving and memory after a single dose of EPO.

EPO receptors have been demonstrated not only in the bone marrow, spleen, liver and brain but in many other organs such as the small bowel. EPO has been shown to protect against necrotizing enterocolitis in newborn rats. Similar findings in other organs point to an overall protective effect.

In a randomized placebo controlled trial involving 53 adults after acute stroke it has been shown that EPO in high dose (100'000 U in three doses) is safe and beneficial. Patients who received EPO had better clinical outcome and smaller lesions in the MRI one month after stroke.

In an ongoing trial in asphyxiated term newborns with high dose EPO no safety concerns could be identified up to now, but definitive results are not yet available.

EPO has been proposed for neuroprotection in preterm infants but to our knowledge no clinical studies are currently under way.

## 2.2.2 Pharmacokinetics of EPO

Studies in rats and sheep have shown greater clearances, shorter half-lives, shorter residence times and greater distribution volumes after i.v. bolus of EPO in fetuses and newborns compared to adults. Consequently the recommended dose per kg body weight for prevention of anaemia is higher in preterm infants than in adults.

Single dose pharmacokinetics of EPO have been studied in preterm infants after intravenous and subcutaneous administration. Mean ( $\pm$ SD) volume of distribution was 300 ( $\pm$ 72) ml/kg, total body clearance 27 ( $\pm$ 9) ml/h\*kg, half life 8 ( $\pm$ 3) hours and maximum serum concentration 711 ( $\pm$ 166) U/l after 200 U/kg i.v. In the stroke trial serum levels rose to 5649 ( $\pm$ 903) mU/ml after the third dose of 33'000 U i.v. resulting in cerebrospinal fluid concentrations of 17.1 ( $\pm$ 5.6) mU/ml which is 60 to 100 times that of non-treated patients.

To be neuroprotective EPO must cross the blood-brain barrier. This has been shown to occur in rats after experimental brain injury and in sheep and nonhuman primates. Juul et al showed a huge increase of endogenous EPO after asphyxia in the cerebrospinal fluid in human newborns (225 $\pm$ 155 mU/ml, range 7 to 2350 mU/ml) compared to control infants (6 $\pm$ 1 mU/ml).

The minimal effective dose for neuroprotection in preterm infants is not known. In the adult stroke trial 100'000 IU EPO divided in three doses were given intravenously and were safe and effective. In rats 5'000 U/kg had the same effect as 10'000 U/kg, both were well tolerated (REF Wang 2004). We consider a dose of 3'000 U/kg as sufficient to achieve a CSF concentration of 5U/ml assuming a Serum/CSF ratio of 100 to 1000.

Recently new derivatives of EPO have been engineered. Darbepoetin- $\alpha$  has 3-fold longer half-life than epoetin- $\alpha$ . Carbamylated EPO and asialerythropoietin are tissue protective but not erythropoietic. These substances are not yet established in clinical routine and their specific properties, e.g. longer survival and lack of erythropoietic effect, have no advantage over the classical EPO in preterm infants.

## 2.2.3 Target Population

Very preterm infants often have significant delay in mental and physical development assessed at 24 months corrected age (Figure 1). Known causal factors are chorioamnionitis and hypoxic-ischaemic events before, during and after birth. Even in preterm infants without documented perinatal risk factors cerebral development may be impaired.

Figure 1:

Developmental outcome in 435 preterm infants born in 2000 in Switzerland before 32 gestational weeks at 24 months corrected for prematurity. Mean Developmental Quotient for infants born at term is 100.

(Swiss Neonatal Network)

[figure not shown]

Furthermore very preterm infants are at high risk of developing intraventricular haemorrhage, white matter injury, retinopathy, persistent ductus arteriosus, bronchopulmonary dysplasia, septicaemia and necrotising enterocolitis.

### **3 Study Objectives**

#### **3.1 Hypothesis**

Early administration of EPO in very preterm infants reduces perinatal injury to the brain, eye, lung and gut and improves neurodevelopmental outcome at 24 months corrected age.

#### **Primary Objective**

To determine whether cerebral outcome is improved if infants born between 26 /7 and 31 /7 gestational weeks at birth receive erythropoietin in high dose in the first three days after birth.

#### **Definition of the Primary Objective**

Primary endpoint: At 24 months of age corrected for prematurity Bayley Scales of Infant Development (BSID-II) and the presence or absence of impairment of motor function (cerebral palsy) and neurosensory function (blindness or deafness) will be assessed.

#### **Secondary Objectives**

To determine whether early administration of erythropoietin alters the incidence of complications typically associated with preterm birth, i.e. mortality, septicaemia, necrotising enterocolitis, bronchopulmonary dysplasia (oxygen dependency at 36 weeks postmenstrual age), retinopathy, intracranial haemorrhage, white matter disease (periventricular leucomalacia), hypertension, growth failure or cerebral palsy and brainvolume at 40 weeks postmenstrual age (MRI).

To evaluate cognitive and fine motor function, vision, hearing and behaviour at five years corrected.

An ancillary economic evaluation is planned in a separate study.

### **4. Study design**

#### **Design**

This randomized trial will be double-masked and placebo-controlled. It will use established definitions for tests accepted and introduced within the Swiss Neonatal Network & follow-up group.

#### **Randomisation**

EPO as a verum is compared to NaCl 0.9% as a placebo 1:1.

Randomisation lists for block randomisation with variable block length will be created by Dr. [name] and provided only to the Kantonsapotheke Zurich (Dr. [name]) involved in production of the medication.

#### **4.3 Study duration**

The study is scheduled to begin on 01 January 2006. The in-hospital phase of the study will last minimum 8 weeks, maximum 14 weeks (until 40 completed weeks of gestation). All patients will

be followed up for developmental outcome at 24 months after term and at five years. Therefore the whole study will last five years for each participating child.

## **5. Study Population**

### **Recruitment**

To determine whether early administration of EPO alters the incidence and severity of complications typically associated with preterm birth in infants born between 26 /7 and 31 /7 gestational weeks at birth patients were examined to their suitability for this study in terms of the inclusion and exclusion criteria.

### **5.2 Inclusion criteria**

1. Infants born between 26 /7 and 31 /7 gestational weeks
2. Postnatal age less than 3 hours
3. Informed parental consent (preferably obtained before birth)

### **5.3 Exclusion criteria**

1. Genetically defined syndrome
2. Severe congenital malformation adversely affecting life expectancy
3. Severe congenital malformation adversely affecting neurodevelopment
4. A priori palliative care
5. Intracranial haemorrhage grade 2 or more detected before dose 3 of EPO

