| Primary Objective           | Mental development at 24 months (Bayley II)                                                                                                                                                                                                                                                                                                                                                                                                                                                                                                                                                                                 |
| Secondary Objectives        | 
 
1. Incidence of intracranial haemorrhage
 
2. white matter disease (periventricular leucomalacia)
 
3. septicaemia
 
4. necrotising enterocolitis
 
5. persistent ductus arteriosus (PDA)
 
6. bronchopulmonary dysplasia
 
7. retinopathy
 
8. Length of stay in hospital
 
9. Cerebral volume at 40 postmenstrual weeks (MRI)
 
10. Weight, length and head circumference at 40 postmenstrual weeks and 24 months after term
 
11. Incidence of visual, hearing and motor impairment at 24 months
 
 |
| Inclusion Criteria          | 
 
1. Infants born between 260/7 and 316/7 gestational weeks
 
2. Postnatal age less than 3 hours
 
3. Informed parental consent (preferably obtained before birth)
 
                                                                                                                                                                                                                                                                                                                                                                      |

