| Exclusion Criteria          | 
 
1. Genetically defined syndrome
 
2. Severe congenital malformation adversely affecting life expectancy
 
3. Severe congenital malformation adversely affecting neurodevelopment
 
4. A priori palliative care
 
5. Intracranial haemorrhage grade 2 or more
 
                                                                                                                                                                                                                                                                                  |
| Investigational drug        | Human erythropoietin, intravenous application Dosage: 3000 U/kg of body weight, Administered three times, at 3 hours, 12 to 18 hours and 36 to 42 hours after birth.                                                                                                                                                                                                                                                                                                                                                                                                                                                        |
| Comparison therapy          | NaCl 0.9%, same administration route and volume as investigational drug                                                                                                                                                                                                                                                                                                                                                                                                                                                                                                                                                     |

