| Placenta Histology                 |                       | o           |             |                             |                |                   |                                     |
| Ventilation/CPAP            |                       |             |             |                             |                |                   |                                     |
| Respiratory support                | •                     | •           | •           | •                           |                |                   |                                     |
| Ventilation parameters             | •                     | •           | •           | •                           |                |                   |                                     |
| Diagnostics                 |                       |             |             |                             |                |                   |                                     |
| Epo concentration      | •                     |             |             |                             |                |                   |                                     |
| Cerebral ultrasound                | •                     | •           | •           | •                           | •              |                   |                                     |
| Chest X-ray                        |                       | •           | o           | o                           | o              |                   |                                     |
| Brain MRI                          |                       |             |             |                             |                | o                 |                                     |
| Serum, csf cultures                | o                     | o           | o           | o                           |                |                   |                                     |
| Therapy                     |                       |             |             |                             |                |                   |                                     |
| Antibiotics                        | •                     | •           | •           | •                           |                |                   |                                     |

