### **Blinding, Packaging, Storage Instructions, Labelling, Shelf Life**

EPO or an equivalent volume of normal saline (NaCl 0,9%) placebo will be administered intravenously before 3 hours, at 12-18 and at 36-42 hours after birth. A single dose consists of 25 µg (3000 IU) human erythropoietin per kilogram body weight dissolved in 1 ml aqua dest. 1 ml per kilogram birth weight (not the actual weight) will be given intravenously within 3 minutes. The maximal dose is 37.5 µg (4500 IU) for infants weighing 1.5 kilograms or more. The packaging, blinding, labelling and storage of the medicine at the pharmacy conforms to the HMG, according to a randomisation list that is only known to the pharmacy.

The individual vials will be allocated unequivocally by their labelling (centre, patient number). Upon request, 1 container per patient will be supplied, allowing 3 days of treatment. Adequate refrigeration (+2 to + 8°C) must be provided during storage at the individual centres, as well as during shipment to the centres. The filled containers have a shelf life of at least 1 week in unopened condition, and are microbiologically innocuous. Unused samples must be stored by the individual centres until the end of the study, and then discarded at the centre in accordance with the monitors' instructions. Disposal of samples must be documented in a disposal protocol (included in the investigator's file).

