## **7. Study Procedures and Examination Methods**

### **Inclusion in the Study, Beginning of Study**

All patients will be assessed with regard to inclusion/exclusion criteria (sections 5.2 and 5.3). If the criteria are met, the patient shall be included in the study after parental consent has been obtained, and treatment shall immediately be initiated.

The study medication will be obtained from the responsible pharmacy (cf. 6.2). It will be supplied on request. The study centres will be randomised separately.

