### Methods for Assessing Efficacy

Primary endpoint: At 24 months of age corrected for prematurity Bayley Scales of Infant Development (BSID-II) and the presence or absence of impairment of motor function (cerebral palsy) and neurosensory function (blindness or deafness) will be assessed.

Secondary endpoints:

- ultrasound of the brain will demonstrate if Epo reduces the incidence of brain damage, specified as intracranial haemorrhage graded after Papile, ventricular dilatation and white matter disease (periventricular echodensities).
- the occurrence of mortality, septicaemia, necrotising enterocolitis, bronchopulmonary dysplasia (oxygen dependency at 36 weeks postmenstrual age) and retinopathy will be documented in each infant.

- MRI at 40 weeks to assess (a) increased myelinated white matter volume (by quantitative volumetric MRI) (b) microstructural development (by diffusion tensor MRI) of cerebral white matter and (c) cortical and subcortical (basal ganglia) gray matter volume (by quantitative volumetric MRI). This examination will only be optional.

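### Exclusion criterion 5 can be met after randomisation and one or two doses, by an event that is itself a trial endpoint, and the protocol does not say whether such infants stay in follow-up and analysis

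*Protocol*

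**What the plan says.** - **The criterion.** Section 5.3, item 5, reads "Intracranial haemorrhage grade 2 or more detected before dose 3 of EPO". The same item in the synopsis reads only "Intracranial haemorrhage grade 2 or more", with no time limit.
- **The clock.** The research plan in section 2.1 states that "420 infants will be randomized during the first three hours of life". Section 6.2 has study drug given "intravenously before 3 hours, at 12-18 and at 36-42 hours after birth".
- **When eligibility is checked.** The time table (1.6) marks the exclusion criteria only in the column before the start of study. Section 7.1 says "All patients will be assessed with regard to inclusion/exclusion criteria (sections 5.2 and 5.3", and has treatment start at once when the criteria are met and consent is given.
- **Haemorrhage as an outcome.** The first secondary objective in the synopsis is "Incidence of intracranial haemorrhage". Section 8.2 says that "ultrasound of the brain will demonstrate if Epo reduces the incidence of brain damage, specified as intracranial haemorrhage graded after Papile".
- **The scan.** The time table marks "Cerebral ultrasound" as compulsory before the start of study, and the first assessment box in the study diagram (1.7) pairs it with the entry criteria. The research plan and section 7.2 place the first scan only on day 1.
- **What happens afterwards.** Section 4.3 foresees 24-month and five-year follow-up for all patients. The three withdrawal criteria in 7.5 do not name haemorrhage, although a protocol violation is one of them. Section 9.2 defines no analysis population.

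**The concern.** An eligibility criterion should rest on what is known before allocation. This one can be triggered by something that happens under study drug, and the trial's own hypothesis is that study drug changes it. Masking does not protect against this: if EPO alters early bleeding, the arms lose different infants even when nobody knows the allocation.

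Two comparisons are exposed. The haemorrhage endpoint could lose the early grade 2+ cases that it exists to count. The 24-month MDI comparison could lose any effect that runs through early haemorrhage, or acquire a spurious one if haemorrhage marks infants who would have scored low anyway. An analysis plan can keep such infants in the analysis set, but it cannot recover a 24-month assessment that a centre never made because it took the child to be excluded.

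**Working it through.** **Step 1: the window.** Randomisation falls at 0-3 h and dose 3 at 36-42 h. The shortest interval is 36 − 3 = 33 h and the longest is 42 − 0 = 42 h. For about 33 to 42 hours after randomisation, criterion 5 can still be met, in an infant who has had dose 1 or doses 1 and 2.

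**Step 2: the places side by side.** Section 5.3 keeps the criterion open until dose 3. The time table and 7.1 close all criteria before dose 1. The synopsis gives no time. A check completed before dose 1 cannot apply a criterion that runs to dose 3, so these places must be reconciled.

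**Step 3: the planned size, for scale.** The synopsis gives 176 per group (two-sided alpha 0.05, power 0.80) and a total of 420. The readable text gives no effect size, so it can only be back-solved. With d = 0.30 SD, n = 2 × (1.960 + 0.842)² / 0.30² = 174.4, so 175 per arm; the t-test solution is 175.4, so 176. At the test-norm SD of 15 (section 7.8), 0.30 SD is 4.5 MDI points. Then 2 × 176 = 352, and 1 − 352/420 = 0.162, so 420 allows for about 16% loss.

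**Step 4: possible bias in MDI.** None of these inputs is in the protocol; all are assumptions. Early grade 2+ haemorrhage occurs in pC = 5-10% of placebo infants and pE = pC × RR on EPO, with RR from 0.5 to 2.0. The MDI deficit D is 10-20 points. Differences are EPO minus placebo.

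- Case A: haemorrhage causes the deficit and EPO has no other effect on MDI. All randomised: D × (pC − pE). After exclusion: 0.
- Case B: haemorrhage only marks infants who would score D lower anyway, and EPO has no effect on MDI. All randomised: 0. With f the larger of pC and pE, after exclusion: D × [(f − pC)/(1 − pC) − (f − pE)/(1 − pE)].

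| pC | pE | D | A: all randomised → after exclusion | B: all randomised → after exclusion |
|---|---|---|---|---|
| 5% | 2.5% | 10 | +0.25 → 0 | 0 → −0.26 |
| 10% | 5% | 20 | +1.00 → 0 | 0 → −1.05 |
| 10% | 10% | any | 0 → 0 | 0 → 0 |
| 5% | 7.5% | 10 | −0.25 → 0 | 0 → +0.26 |
| 10% | 20% | 20 | −2.00 → 0 | 0 → +2.22 |

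Last row: A is 20 × (0.10 − 0.20) = −2.00; B is 20 × (0.20 − 0.10)/(1 − 0.10) = +2.22. In both cases exclusion works against EPO if EPO lowers early haemorrhage, and in its favour if EPO raises it. If EPO leaves early haemorrhage unchanged, there is no bias.

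**Step 5: power.** Assume that a share r of the 420 is removed and the same 16.2% is then lost, so n per arm = 420 × (1 − r) × 0.838 / 2. With d = 0.30:

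| r | removed | n per arm | power |
|---|---|---|---|
| 3% | 13 | 171 | 0.79 |
| 5% | 21 | 167 | 0.78 |
| 10% | 42 | 158 | 0.76 |
| 15% | 63 | 150 | 0.74 |

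These figures probably overstate the loss, because some infants with early severe haemorrhage would be among the deaths and losses already allowed for.

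**The case against.** The strongest reply is that the protocol never says these infants leave the trial. Section 4.3 has all patients followed, 7.5 does not list haemorrhage, and the analysis set may be defined in a statistical analysis plan that is not shown. The phrase in 5.3 could have been meant as a rule about further dosing, with the infant kept in the cohort. This stands as far as it goes: a reader might infer that an outcome decides who is analysed, and the text does not establish that. But the phrase sits in the list of exclusion criteria, and no sentence keeps the infant in. By contrast, section 7.4.5 says expressly that an infant whose parents decline MRI remains in the cohort.

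A reader might also infer that harm from early bleeding would be hidden. That is too strong. Adverse events are compulsory items from days 1-3, serious ones reach the sponsor within 24 hours (8.5), the safety board monitors continuously with a stopping threshold of p < 0.01 (8.1), and a report follows the first 45 patients (9.3). What is exposed is the efficacy tabulation of haemorrhage, not all knowledge of it.

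Two smaller replies have some force. The synopsis may simply have shortened the criterion; the harder conflict is with the time table and 7.1. And the body text, which times the first scan only as day 1, does not clearly require a scan before randomisation, so a purely pre-randomisation criterion needs that wording aligned.

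**Conclusion.** The point holds on timing and text alone. Criterion 5 as written in 5.3 can be met after randomisation and after study drug has been given, by an event that the trial also counts as an outcome, and it contradicts the places that put eligibility before treatment. Applied as an exclusion, it can deplete the haemorrhage endpoint and bias the MDI comparison.

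The size is not derivable from the protocol. Under the assumptions above it runs from 0 to about 2 MDI points in either direction, against a back-solved detectable difference of about 4.5; it is 0 if EPO does not affect early haemorrhage. A narrower bias range, or a single direction, would rest on unsupported choices of rate and mechanism. Loss of power is a minor matter and is not the reason to act. That infants are actually dropped from follow-up or analysis is an inference from the word exclusion; the defect that can be shown is that the protocol leaves their status open.

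**What to change.** - Reconcile the synopsis, the time table, 5.3 and 7.1 so that criterion 5 refers only to a haemorrhage of grade 2 or more found before randomisation. Base it on the pre-study ultrasound that the time table already marks as compulsory, and align the day 1 wording in the research plan and 7.2 with it.
- State that a randomised infant with a haemorrhage found later counts in the haemorrhage endpoint, is followed to 24 months and is analysed in the allocated arm.
- Seek the 24-month assessment for any infant already removed under this rule, and include those infants. Section 9.2 places the analysis between spring 2009 and spring 2013, so some of these data may still be obtainable.

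Whether study dosing continues after a haemorrhage is a separate clinical matter on which no view is given here.

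The cost is an amendment, which under 11.3 goes to the ethics committee and the authorities, plus follow-up of any infants already removed; the protocol does not show how many there are. If some centres make the first scan only after dose 1, bringing it forward would be an added demand on them.
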